## Statistical Analysis

### Demographic Data

Measures of central tendency for various demographic variables (age, height, weight etc.) will be provided. Other baseline data including laboratory evaluations and medical history will be tabulated.

### Efficacy Analysis

**Efficacy Endpoints**: Proportion of patients achieving

- Initial cure (splenic aspirate score on Day 30 and 45)
- Clinical improvement on Day 30 after first dose of study drug
  - Absence of fever; and >1 out of following:
    - Increase in hemoglobin concentration by ≥10% compared to baseline
    - Weight gain compared to baseline visit
    - Decrease in spleen size by >33% compared to baseline
- Definitive cure:

1. Initial cure at Day 30 or Day 45
2. No clinical signs and symptoms of relapse of Kala-azar for 6 months after study drug administration. If clinical signs and symptoms of relapse of the disease is suspected at any time during the 6 month follow up, splenic aspirate shall be performed at 6 months or earlier after study drug administration.

Proportion of patients achieving all three-efficacy endpoints will be compared across the two groups.

**Primary Efficacy Analysis:**

Non-inferiority will be assessed by looking at the lower end of a two sided 95% confidence interval (CI) of the difference Ptest - Pref (the difference in the proportions of patients achieving definitive cure in Amphomul^®^ (Ptest) and AmBisome (Pref). Non-inferiority will be only accepted if the lower limit of the two-sided 95% CI is greater than the non-inferiority margin of -0.10.

Non-inferiority will be tested for both MITT and PP population.

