## 11.2 Sample Size

Considering an estimated difference in proportions of patients achieving definitive cure for Amphomul^®^ vs. AmBisome equals to zero and non-inferiority margin fixed at -0.10, a sample size of 400 patients in ratio of 3:1 in Amphomul^®^ and AmBisome treatment groups (i.e. 300 patients in Amphomul^®^ and 100 patients in AmBisome) is required to assure at least 80% power for the non-inferiority test. Considering a total drop out rate after baseline and major protocol deviations close to 20%, 500 patients (i.e. 375 patients in Amphomul^®^ and 125 patients in AmBisome) will be enrolled in the study.

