## Randomization and Blinding

- Since this is an open label study, blinding is not applicable.
- Permuted Block randomization schedule with block of size 4 and ratio of 3:1 in the two groups (Amphomul and AmBisome) will be generated for each center.
- Treatment with IP/Comparator drug will begin only after successful screening (signing informed consent and fulfillment of all eligibility criteria).
- After meeting eligibility criteria, the patient will sequentially be allotted to unique subject ID and treatment as per randomization schedule for that center.
- A separate screening and enrolment log will be maintained.
- Neither the Investigators nor patient/patient’s LAR will be blinded to the treatment regimen.

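### Randomisation is stratified by centre but the primary non-inferiority interval is stated without centre; stratifying it would be a small gain in precision at no cost

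*Protocol*

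**What the plan says.** **Randomisation.** Section 15.3 specifies a "Permuted Block randomization schedule with block of size 4 and ratio of 3:1 in the two groups" and says that it "will be generated for each center". Section 13 (Visit 1, Day 1) repeats this. The Study Summary gives four centres.

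**Primary analysis.** Section 20.2.2 takes Ptest - Pref, "the difference in the proportions of patients achieving definitive cure", and accepts non-inferiority only if the "lower limit of the two-sided 95% CI is greater than the non-inferiority margin of -0.10". The rule applies to both MITT and PP. Centre is not mentioned there or elsewhere in section 20, and no interval method is named. Section 20.2.4 promises only suitable tests in SAS.

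**Sample size.** Section 11.2 (repeated in 12.1) assumes a true difference that "equals to zero and non-inferiority margin fixed at -0.10". It states that "a sample size of 400 patients in ratio of 3:1", that is 300 and 100, "is required to assure at least 80% power for the non-inferiority test". Enrolment is 500 to allow for 20% losses and major deviations. No overall or centre-specific cure rate is given, and no gain from stratification is claimed.

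**The concern.** Blocking 3:1 within each centre balances the arms on everything that differs between centres, so between-centre variation in cure does not enter the treatment comparison. A standard error computed from two pooled proportions puts that variation back. The estimate does not move, but the lower limit that decides the trial sits a little further down than the design requires.

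Centre differences are plausible, though undocumented. Sections 8 and 19 have all samples analysed at local laboratories, section 19 allows either of two stains and independent checking of slides from only 10% of patients, and the six-month outcome is judged clinically unless relapse is suspected.

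The stake is a little power. With about 100 comparator patients the half-width is about 0.07, so a small shift matters only if the lower limit falls close to -0.10. Because the trial is open-label, a choice between pooled and stratified intervals made late could also look data-driven in such a case.

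**Working it through.** **Inputs.** From the protocol: 300 v 100 evaluable patients, 3:1 within each of four centres, true difference 0, margin -0.10, two-sided 95% interval (one-sided 0.025), 80% power. Assumed: centre cure rates, and equal centres (75 v 25 each).

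**Step 1: the plan's own figure.** With a common cure rate p and no centre term, the comparator arm needs

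n = (1.960 + 0.842)² × p(1 - p) × (1 + 1/3) / 0.10².

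At p = 0.893: 7.849 × 0.09555 × 1.3333 / 0.01 = 100, hence 100 + 300 = 400. At p = 0.90 the total is 380, and 400 gives 82.3% power. At p = 0.85 it is 536. Then 400 / (1 - 0.20) = 500. So 400 fits an unstratified calculation at an assumed cure rate near 0.893, and the planned power does not rely on stratification.

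**Step 2: what stratification changes.** With exact 3:1 in every centre the pooled and Mantel-Haenszel point estimates are identical. Only the variance differs:

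p̄(1 - p̄) = mean of p_c(1 - p_c) + between-centre variance of p_c.

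The unstratified interval uses the left side and the stratified one uses only the first term on the right. The half-width is 1.96 × √(that quantity × (1/300 + 1/100)).

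Example, 80/90/95/98%: p̄ = 0.9075 and p̄(1 - p̄) = 0.08394. The within-centre mean is (0.1600 + 0.0900 + 0.0475 + 0.0196)/4 = 0.07928, a ratio of 0.944.

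| Assumed centre cure rates | Within/total variance | Half-width, unstratified | Half-width, stratified |
|---|---|---|---|
| 89.3% in all | 1.000 | 0.0700 | 0.0700 |
| 85/90/95/97% | 0.971 | 0.0623 | 0.0614 |
| 80/90/95/98% | 0.944 | 0.0656 | 0.0637 |
| 75/90/95/100% | 0.903 | 0.0679 | 0.0645 |

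The narrowing is 1 - √ratio: 0, about 1.4%, 2.8% and 5.0%.

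**Step 3: operating characteristics.** Simulation, 200,000 trials per scenario. Power is at a true difference of 0; one-sided error is at -0.10 in every centre. The unstratified interval is Wald. The lower and upper ends of the gain come from n-1 and Sato variances, and the stratified error shown is for Sato.

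| Assumed centre cure rates | Power, unstratified | Gain from stratifying (points) | Error, unstratified | Error, stratified |
|---|---|---|---|---|
| 89.3% in all | 83.5% | 0.1 to 0.2 | 1.85% | 1.85% |
| 85/90/95/97% | about 92.9% | 0.4 to 0.7 | 1.6% | 1.7% |
| 80/90/95/98% | 89.5% | 1.2 to 1.7 | 1.5% | 1.8% |
| 75/90/95/100% | 87.3% | 2.4 to 2.9 | 1.4% | 1.8% |

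**Step 4: the choice of variance matters.** A plain within-centre Wald variance with n as divisor moves power from 83.5% to 84.5% when all centres are identical, where stratifying cannot help. That point is variance underestimation with 25 comparator patients per centre, not precision gained, so this form should not be used to judge or obtain the benefit.

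**The case against.** The strongest reply is that section 20.2.2 fixes a parameter, a confidence level and a margin, but no method. A Mantel-Haenszel or stratified score interval is also an interval for Ptest - Pref and would comply with the text as it stands. Interval method and stratification factors are ordinary content for a statistical analysis plan, and that document is not at hand. This stands: a reader might infer that the protocol prescribes a crude interval, but it never says so. An unstratified interval is only the natural reading of a rule that leaves centre out.

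A reader might also infer that the test departs seriously from its nominal level because the strata are ignored. The figures do not support that. One-sided error is already 1.85% with identical centres, so much of the gap to 2.5% comes from Wald limits in this setting, which the protocol does not prescribe either. Leaving out the strata makes the test more conservative and cannot make a false non-inferiority claim more likely.

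The premise is also conditional. Without centre differences there is essentially nothing to gain, and the largest effect needs one centre at 75% and another at 100%. This stands as well.

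What remains is that the primary decision rule is written in the protocol, its randomisation stratum is absent from it, and the stratified interval costs essentially nothing when centres are alike.

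**Conclusion.** The point holds as a minor improvement. Centre is a randomisation stratum and the primary interval is stated without it. Read as unstratified, the interval is up to about 5% wider than needed under the assumed rates, which costs roughly 0 to 3 power points. There is no bias and no type I inflation. It would be wrong to infer that the trial is underpowered for this reason: 400 fits an unstratified calculation at a cure rate near 0.893, and simulated power exceeds 80% in all four scenarios with or without stratification.

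The sizes rest on assumed centre rates, equal centres and exact 3:1 within each centre. Incomplete last blocks and the expected 20% losses would disturb that balance slightly, so in practice the two point estimates would be close rather than identical.

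**What to change.** Add one sentence to section 20.2.2: the two-sided 95% interval for Ptest - Pref is stratified by centre, using the Mantel-Haenszel weighted risk difference with Sato variance or a stratified score interval (one of the two, named in advance), for both MITT and PP. Rule out the plain n-divisor within-centre Wald variance. Report the unstratified difference and its interval as supportive.

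The margin, confidence level and sample size are unchanged. No extra patients or data are needed. If the statistical analysis plan already says this, a cross-reference is enough.

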**Secondary Efficacy Analysis**:

The proportions of patients achieving initial cure, clinical improvement in both treatment arms will be tabulated along with two-sided 95% confidence interval for both MITT and PP population

### Safety Analysis

Safety Endpoints:

- - Incidence of DLTs
  - Incidence of IRTs
  - Incidence of nephrotoxicity and hepatotoxicity
  - Incidence and frequency of AEs and SAEs (including laboratory abnormalities)

The safety analysis will be performed on the ITT population. Proportion of patients experiencing DLTs, IRTs, nephrotoxicity, hepatotoxicity, AEs and SAEs will be tabulated. Laboratory data will be summarized and displayed, including abnormal values judged to be clinically significant.

SAE reports will be presented individually. AE data will be listed individually, coded using Medical Dictionary for Regulatory Activities (MedDRA) enhanced version. Each AE will be counted only once for a given patient. If the same AE occurs on multiple occasions, the highest severity and relationship will be assumed. If two or more AEs are reported as a unit, the individual terms will be reported as separate experiences.

Concomitant medications will be coded by using the World Health Organization Drug Dictionary (WHODD) Reference List enhanced version.

Vital sign data, physical examination results, ECG examinations results will be summarized for ITT population

### Statistical Analysis of Data

SIRO Clinpharm Pvt. Ltd will perform the statistical evaluation using appropriate statistical tests. Statistical analysis will be performed using SAS^®^ software (SAS Institute Inc., NC, USA).

# 21. PROTOCOL MODIFICATIONS, DEVIATIONS and AMENDMENTS

The Sponsor may at any time modify the Protocol, after approval by Investigator and, if required, by IRB.

## Deviations for a particular patient

When a deviation from the protocol is deemed necessary for an individual patient, the Investigator must contact one of the monitors. Such contact with the monitor must be made as soon as possible to permit a decision as to whether or not the patient is to continue the study; any departure from the protocol will be authorized only for that patient. In the event of any drug-related toxicity, all possible measures should be taken to protect well being and life of the patient, notwithstanding the possibility of dropout from the study and regardless of contact with/permission from any other member involved in the trial. A description of the departure from the protocol and the reason(s) for it must be recorded in the CRF for such patients.

## Amendments, if any for the study

### Administrative modifications

Administrative or technical modifications (like change in monitor or telephone numbers), which do not interfere with the patient's health interests will be in writing and filed as amendments to the protocol. The IEC/IRB has to be informed by the PI regarding every such amendment.

### Clinical modifications

Modifications, interfering with the patient's health interests and involving changes in the design of the study or its scientific significance require a new approval of the IEC/IRB. The Sponsor and investigator will agree to implement/adhere to such modifications.

# 22. ADMINISTRATIVE MATTERS- ADHERENCE TO GOOD CLINICAL PRACTICE (GCP) GUIDELINES

## Regulatory requirements

DCGI acts as the nodal office for approval of clinical trial applications. The study will be started only after notifying DCGI.

## Ethics Committee

The study will be started at the institute only after approval from the IEC/IRB.

## Investigator Qualification

Any physician who is assigned PI of a clinical study must have professional integrity, must be familiar with the requirements of clinical studies and must be trained and experienced in the performance of clinical studies. A curriculum vitae*,* outlining the Investigator’s educational and professional qualification, has to be provided to the sponsor.

## Clinical Supplies and Storage

The Investigator will be provided with adequate quantities of the following material to permit completion of the study:

1. IB
2. Latest version of the study Protocol
3. CRFs
4. ICFs
5. IPs

The Investigator should maintain adequate records of the receipt and disposal of all IP supplied. Any unused medication will be returned to SIRO at the conclusion of the study. The Investigator should ensure that the IP is stored in a limited access area and protected from extremes of light, temperature and humidity.

## Data Collection, Documentation and Archiving of Study Documents

The required data have to be recorded in the CRF by the Investigator in anonymous form. Data listings must be generated from the original data of the CRF. In the medical report, it should be noted that the patient is participating in a clinical study and the study code and IP must be listed. All data and information on the study patient, laboratory values, and efficacy parameters have to be documented in the source data by the PI or designee. Patient data in the CRFs are coded in a way to enable easy tracking of the original patient data.

The CRF records must be complete and legible. The entries must be done using a black ink ballpoint pen. Any correction and modification must be entered, initialed and dated by staff authorized by the Investigator. Incorrect entries are not allowed to be obliterated by using e.g. Tipp-Ex^®^, eraser, white ink etc. Errors must remain readable.

**Patient and Medication Logs**

All patients coming to the investigational centre for the study indication during the course of the study will be recorded and numbered in a patient log. Only those patients, who fulfill the eligibility criteria, will be included in the study.

The Investigator is obliged to list all deliveries of IP in a medication log, thus documenting all deliveries of the sponsor and medication administered to the patients. The SIRO monitor will account for all used and unused drug supplies during the periodic monitoring visits, and supplies, as appropriate, would be retrieved. After termination of the study, samples, which have not been used, and the medication log must be returned to SIRO Clinpharm Pvt. Ltd. for control counting.

## Study Initiation

After the IEC approval is available, a “Site Initiation Visit” will be held before the first patient is enrolled on the study. The patients cannot be recruited until occurrence of such visit and its documentation. During this visit requirements of GCP, protocol procedures and all logistic issues will be discussed at length. The training of Investigator team will be documented.

## Study Monitoring and Source Data Verification

After the study is initiated, SIRO Clinpharm Pvt. Ltd. monitor(s) will take up contact with the Investigator to obtain information on the performance of the study. These contacts will be scheduled to take place at regular intervals and be either in person or telephonic.

These monitoring visits will take place at least 9 times during the entire study. The monitoring visits will be with an interval of 4-6 weeks followed by a close out visit at the end of the study.

Subsequent to start of recruitment, the first ***“*Routine Monitoring Visit”** would occur as soon as possible after recruitment of the first patient.

**Subsequent 2 Visits** would generally occur at an interval of 4 weeks while the **remaining visits** would occur at an interval of 4-6 weeks till end of study (after prior appointment with the Investigators).

The Investigator and his/her staff are obliged to set aside adequate time and place for the monitoring visits. During each monitoring visit, the monitor will review the CRFs of each patient in the study with regard to completeness, thoroughness and compliance to the protocol.

All hospital records/other records where original entries are made will be reviewed to make sure that-

1. Patient informed consent is incorporated
2. Inclusion/exclusion criteria are properly fulfilled
3. The CRF data are consistent with the physician's original records, which also have to clearly indicate that the patient is included in a clinical study
4. All relevant clinical and laboratory findings and concomitant medication are documented in the CRFs
5. Quantity and dosing schedule of concomitant medication is documented in the CRF
6. Quantity and dosing schedule of the IP/Comparator Product is in accordance with the protocol
7. All relevant information (e.g. any AE) has been recorded in the appropriate place in the CRFs
8. The IP/Comparator Product is being stored correctly, and its supply being properly accounted for
9. Incorrect or illegible entries in the CRFs would be submitted to the Investigator for correction.

The SIRO monitor will retrieve completed CRFs during the regularly held monitoring visits.

During the entire course of the study the responsible SIRO staff will be available to answer questions with regard to the performance of the study.

## Record Retention

All documentation pertaining to the study will be kept by Bharat Serums and Vaccines Ltd. for the lifetime of the product. The final report pertaining to this study will be kept by Bharat Serums and Vaccines Ltd. for a further five years.

The study monitor will provide each Investigator with a Site Master File*,* which should be used to file the IB, protocol, drug accountability records, correspondence with the IRB/IEC, Bharat Serums and Vaccines Ltd., SIRO and other study-related documents.

As required by ICH GCP guidelines, the Investigator must keep essential documents until at least 2 years after the last approval of a marketing application in an ICH region, and until there are no pending or contemplated marketing applications in an ICH region, or at least 2 years have elapsed since the formal discontinuation of clinical development of the IP.

These documents should be retained for a longer period, however, if required by the applicable regulatory requirement*(s)* or if needed by the Sponsor. In addition, the Investigator must make provision for the patient’s medical records to be kept for the same period of time.

No data should be destroyed without the agreement of the Sponsor Bharat Serums and Vaccines Ltd. will inform the Investigator in writing of the need for record retention and will notify the Investigator in writing when the trial related records are no longer needed.

Patients’ medical records and other original data will be archived in accordance with the archiving regulations or facilities of the investigational sites.

## Insurance and Indemnity

In the event that a patient suffers injury or death directly attributable to participation in this study, appropriate treatment and/or compensation will be provided by and/or paid to the patient by the Sponsor in accordance with applicable national laws and/or guidelines.

## Audits and Inspection

In addition to the above outlined monitoring visits, the investigational centres may be audited or inspected. The audit may be carried out by the Quality Assurance Department of SIRO Clinpharm Pvt. Ltd. or Sponsor *(Bharat Serums and Vaccines Ltd.)* or subcontracted by the Sponsor. In addition, regulatory authorities may inspect the study. Patient confidentiality will be maintained at all times to the extent permitted by the law. Audits and Inspections are conducted to assess compliance to the protocol, SOPs, ICH guidelines, regulatory requirements and any applicable guidelines.

The Investigator undertakes to expeditiously inform SIRO Clinpharm Pvt. Ltd. of an inspection requested by a regulatory authority.

## Data Management and Archival

Data management will be performed at SIRO Clinpharm Pvt. Ltd. according to SIRO SOPs. Data items from the CRFs will be entered centrally into the study database by CDM Staff using double data entry with interactive verification upon second entry ensure accurate data entry. Data reviewers & Medical Reviewers will perform a manual review of CRF pages as well as data discrepancies generated by electronic edit check programs. Any discrepancies noted in the data will be sent to site for resolution as data query forms. After all the data queries are resolved the database will be declared to be complete and accurate and will be locked for final analysis.

Copies of CRFs, other original source data related to the study, the site master file (which would contain, among other documents, the Patient Log and ICFs) would be archived until the sponsor requires them to be archived. The sponsor would inform the Investigator when the documents need no longer be retained at the study site.

## Patient Confidentiality and Data Protection

SIRO and Bharat Serums and Vaccines Ltd. will affirm and uphold the principle of the patient’s right to protection against the invasion of privacy. Throughout this study and any subsequent data analyses, all data reported to the sponsor will be identified only by protocol number, patient number and patient initials.

